## Abstract

**Background:**

In contrast to severe gestational hypertension, it is questioned whether antihypertensive medication for mild to moderate gestational hypertension prevents adverse maternal and offspring outcomes. Hypertensive drugs halve the risk of severe hypertension, but do not seem to prevent progression to preeclampsia or reduce the risk of complications in offspring. In fact, beta-blockers, a first line therapy option, are suspected to impair foetal growth. Disappointing effects of antihypertensive medication can be anticipated when the pharmacological mode of action does not match the underlying haemodynamic imbalance. Hypertension may result from 1) high cardiac output, low vascular resistance state, in which beta blockade is expected to be most effective, or 2) low cardiac output, high vascular resistance state where dihydropyridine calcium channel blockers or central-acting alpha agonists might be the best corrective medication. In the latter, beta-blockade might be maternally ineffective and even contribute to impaired foetal growth by keeping cardiac output low. We propose a randomized controlled trial to determine whether correcting the haemodynamic imbalance in women with mild to moderate hypertension reduces the development of severe hypertension and/or preeclampsia more than non-pharmacological treatment does, without alleged negative effects on foetal growth.

**Methods:**

Women diagnosed with mild to moderate hypertension without proteinuria or signs of other organ damage before 37 weeks of pregnancy are invited to participate in this randomized controlled trial. Women randomized to the intervention group will be prescribed tailored antihypertensive medication, using a simple diagnostic and treatment algorithm based on the mean arterial pressure/heart rate ratio, which serves as an easy-to-determine proxy for maternal circulatory state. Women randomized to the control group will receive non-pharmacological standard care according to national and international guidelines. In total, 208 women will be randomized in a 1:1 ratio. The primary outcome is progression to severe hypertension and preeclampsia and the secondary outcomes are adverse maternal and neonatal outcomes.

**Discussion:**

This trial will provide evidence of whether tailoring treatment of mild to moderate gestational hypertension to the individual haemodynamic profile prevents maternal disease progression.

**Trial registration:**

NCT02531490, registered on 24 August 2015.

## Background

Preeclampsia is a leading cause of maternal and perinatal morbidity and mortality in the western world [1]. In most cases of preeclampsia-related maternal death, blood pressure is not adequately controlled [2, 3]. For its well-established maternal benefits, it is generally accepted to treat blood pressure when it reaches the threshold of severe hypertension (systolic or diastolic blood pressure ≥ 160 or ≥ 110 mmHg respectively) [4]. In contrast, effectiveness of antihypertensive medication in mild to moderate hypertension is subject of debate and medication is not uniformly initiated because of different effects on maternal disease progression and alleged poorer foetal outcomes [5, 6]. In mild to moderate hypertension, the use of any antihypertensive drugs halves the risk of developing severe hypertension (relative risk of 0.49; 95% CI 0.40–0.60), but does not prevent progression to preeclampsia (relative risk of 0.93; 95% CI 0.80–1.08), or reduce the risk of offspring complications (relative risk for small for gestation age neonate, 0.97; 95% CI 0.80–1.17, relative risk for stillbirth, 1.14; 95% CI 0.60–2.17 and relative risk for neonatal death, 0.79; 95% CI 0.14–4.34) [6]. On the other hand, sub-grouped by class of drugs, beta-blockers seemed to reduce the development of preeclampsia (OR 0.73; 95%CI 0.57–0.94) but may increase the chance of the neonate being small for gestational age (OR 1.38; 95%CI 0.99–1.92), while calcium antagonists seemed to increase the chance of preeclampsia (OR 1.40; 95%CI 1.06–1.86), but have no effect on foetal growth (OR 0.84; 95%CI 0.60–1.16) [6]. As a consequence of these inconsistent findings when pooling all antihypertensives irrespective of mode of action, international guidelines recommend initiating medication of choice only in severe hypertension or repeated moderate gestational hypertension [7, 8].

A drawback in studies investigating treatment of mild to moderate gestational hypertension is that they do not consider the maternal circulatory state or the circulatory response to the blood pressure lowering drug. Instead, most reported treatments involve stepwise use of compound drug classes, based on the physician’s experience; in this treatment approach, chosen medications are only changed if severe side effects are observed or if increasing dosages do not achieve the target blood pressure. This trial-and-error approach may not only delay the time interval to effective circulatory control, but may also negatively affect foetal wellbeing that may prelude to preterm birth.

Antihypertensive drugs lower blood pressure via different mechanisms. Blood pressure is regulated within narrow boundaries by beat-to-beat baroreceptor-mediated alteration of cardiac output and vascular resistance. Blood pressure only changes when these two determinants are unable to compensate deteriorations; therefore, elevated blood pressure can be lowered by reducing cardiac output or vascular resistance, or both. Beta-blockers, central-acting alpha agonists, and calcium antagonists are commonly used to lower blood pressure during pregnancy. Selective beta-blockers lower elevated blood pressure predominantly by lowering the heart rate (HR) and reducing contractility, resulting in reduced cardiac output. Beta-blockers with additional ɑ-adrenergic receptor blockade activity, like labetalol, concurrently reduce peripheral resistance [9, 10]. Central-acting alpha receptor agonists, like methyldopa, lower blood pressure by altering central sympathetic activity. Cardiac output levels do not change, suggesting a balance between reduced afterload, venous return, and negative chronotropic and inotropic effects of sympathetic inhibition [11, 12]. Dihydropyridine calcium channel blockers, like nifedipine, are relatively vasoselective. They inhibit calcium ions from entering the calcium channels of vascular smooth muscle, so blood pressure is mainly lowered by reducing arterial tone and with it, peripheral vascular resistance. Secondary to vasodilation, the sympathetic nervous system is activated resulting in increased levels of norepinephrine, higher HR and ultimately increased cardiac output [13–15].

### Haemodynamic parameters in gestational hypertension

The haemodynamic profile of gestational hypertension differs between individuals. On the one hand, gestational hypertension can originate from hyperdynamic circulation characterized by high cardiac output and low vascular resistance; this profile is often accompanied by late onset preeclampsia and normal foetal growth (Fig. 1). On the other hand, a hypertensive profile with high vascular resistance is associated with early onset maternal complications and impaired foetal growth [16–19]. In the clinical phase of preeclampsia, most women exhibit a high-resistance profile with either low cardiac output (in 58% of women) or normal cardiac output (in 36% of women) [20]. Altered pre-pregnant haemodynamic phenotypes, inadequate cardiovascular adaptation to pregnancy, or crossover from hyperdynamic circulation to the more unfavourable hypertensive circulation with high vascular resistance as a consequence of endothelial derangement and loss of intravascular fluid, might underlie the divergent haemodynamic profiles [21, 22]. These heterogeneous circulatory profiles may explain the variable results of trials on antihypertensive therapy in mild to moderate hypertension during pregnancy. Beta-blockers are thought to be suitable for treating hyperdynamic hypertension, but reducing cardiac output may be detrimental in hypertensive women with high vascular resistance who already have low-cardiac-output. These women may instead benefit from vasodilation by dihydropyridine calcium channel blockers, or from central-acting alpha agonists that reduce peripheral resistance.

**Fig. 1 Fig1:**
[figure not shown]
Haemodynamic profiles in mild hypertension, associated complications and appropriate antihypertensive treatment

### Tailored treatment of hypertension

In non-pregnant individuals with uncontrolled hypertension, haemodynamically tailored antihypertensive treatment almost doubled the chance of reaching the target blood pressure within 3 months of initiating or adjusting the therapy compared with conventional standard treatment based on the specialist’s preference [23, 24]. During pregnancy, with respect to underlying haemodynamic profile, adequate blood pressure response to beta-blockage can be predicted by the mean arterial pressure (MAP), HR, and (if available) stroke volume index [25]. About 20–25% of gestational hypertensive women were refractory to labetalol and needed additional vasodilatory therapy. In these women, cardiac output was lowest and vascular resistance was highest before treatment. The highest response rate to labetalol primarily relates to alteration of HR and peripheral vascular resistance, and consequently blood pressure, but not stroke volume. This suggests that a simple algorithm weighing blood pressure and HR may grossly indicate the underlying haemodynamic profile. Therefore, it may be better to view antihypertensive drugs as adjusters of the haemodynamic state rather than as reducers of blood pressure [26]. If we do not take the maternal haemodynamic profile and the pharmacological mode of action of the drug into account, generic antihypertensive treatment will continue to result in disappointing, ineffective or even paradoxical outcomes for at least part of treated mothers and their offspring. To address this problem, we propose a randomized trial to compare tailored antihypertensive treatment based on the maternal circulatory profile with generally practiced active surveillance of hypertension in pregnant women with mild to moderate hypertension.

## Methods/design

### Aim

The aim of this study is to determine whether haemodynamically tailored antihypertensive therapy in pregnant women with mild to moderate hypertension reduces the incidence of severe hypertension and preeclampsia and improves offspring outcome compared with standard care.

### Objectives

Our primary objective is to determine whether haemodynamically tailored treatment of mild to moderate hypertension reduces disease progression to severe hypertension and preeclampsia compared with standard care. Our secondary objectives are to assess the effects of this treatment approach on maternal and offspring outcomes, including concomitant HELLP syndrome and eclampsia, gestational age at delivery, and neonatal birth weight and centile.

**Fig. 2 Fig2:**
[figure not shown]
Schedule of enrolment, intervention, and assessments

**Fig. 3 Fig3:**
[figure not shown]
SPIRIT timetable of the study

Participants will be recruited from the outpatient clinic and department of obstetrics in Maastricht University Medical Centre, which is both a secondary and tertiary referring hospital. During every routine pregnancy check-up, blood pressure is measured. Women with mild to moderate hypertension (defined as systolic blood pressure measures ≥140 and < 160 mmHg and/or diastolic blood pressure ≥ 90 and < 110 mmHg) without symptoms or signs of preeclampsia will be given the study patient information form, and follow-up on blood pressure is planned at least 4 h later and within a few days. Eligible women who give consent will be randomized to the intervention or control group, after which they will continue regular pregnancy check-ups with blood pressure measurements; additional laboratory analysis will be performed as indicated. After 37 weeks’ gestation, induction of labour will be recommended to all participants, as this is associated with improved maternal outcome [27]. Study endpoints are an uneventful pregnancy and 6-week postpartum period, or diagnosis of severe hypertension or preeclampsia. In the latter case, participants will receive standard care, which usually means hospitalization and intensifying or initializing antihypertensive medication for the intervention group and control group, respectively.

### Eligibility criteria

Women must provide written informed consent before any study procedure occurs.

#### Inclusion criteria

Patients eligible for the trial must meet the following criteria at randomization:
Age ≥ 18 years;Living foetus before 37 weeks’ gestation;Diagnosed with mild gestational hypertension (systolic blood pressure 140–159 mmHg and/or diastolic blood pressure 90–109 mmHg, measured twice with at least 4 h in between).

#### Exclusion criteria

Severe hypertension (systolic blood pressure ≥ 160 mmHg and/or diastolic blood pressure ≥ 110 mmHg);Diagnosed with preeclampsia, HELLP syndrome, or eclampsia;Taking antihypertensive drugs;Intending to terminate the pregnancy;Foetus has a major anomaly or chromosomal abnormality;Not able to comprehend the study outline;Contraindication for one of the possible prescribed antihypertensive medications.

### Interventions

Eligible patients who consent to participate will be randomized to receive tailored antihypertensive medication (intervention group) or standard care (control group). The antihypertensive medications we plan to administer to participants in the intervention group can be safely prescribed to pregnant women [6]. Total peripheral vascular resistance (calculated as: 80 × MAP / cardiac output) indicates whether the hypertension is cardiac- or vascular-driven. In a healthy pregnancy, total peripheral vascular resistance drops from approximately 1300 to 1000 dyne.s/cm^5^ during the second and third trimester [28, 29]. Considering a standard deviation (SD) of 150 dyne.s/cm^5^, the upper limit of healthy dilated total peripheral vascular resistance is 1300 dyne.s/cm^5^. Women can be considered vasoconstricted when gestational vascular resistance exceeds 1300 dyne.s/cm^5^ and vasodilated when vascular resistance is below 1300 dyne.s/cm^5^. To avoid the need for an additional tool to assess cardiac output (stroke volume × HR), the MAP/HR ratio is used as a proxy for the haemodynamic profile. The MAP/HR ratio differs from total peripheral vascular resistance assessment in that it does not account for stroke volume. During healthy pregnancy, the mean ± SD stroke volume is 75 ± 10 ml. In the estimation of which proportion of women can be assumed to be vasoconstricted or vasodilated using the MAP/HR ratio, we can estimate the range in which total peripheral vascular resistance must be by taking the mean ± 2 SD stroke volume. When the MAP/HR ratio exceeds 1.4, more than 95% of all women must be considered vasoconstrictive. Contrary, when the MAP/HR ratio is 1.1 or less, more than 50% of women are likely to have a vasodilated circulation (Fig. 4). In the absence of empirical data that support the determination of cut-off values, we assumed a likelihood of more than 95% vasoconstrictive and relatively hypodynamic, corresponding a MAP/HR ratio 1.4 as reference value for considering vasodilating medication, and opposite, a likelihood of more than 50% of women to be vasodilated and hyperdynamic, corresponding MAP/HR ratio of 1.1 as a reference value for considering HR-lowering and with it, cardiac output-lowering medication. In the latter case, a beta-blocker with dual alpha- and beta-adrenergic receptor antagonism will account for the potential overlap in profiles. Thus, we will administer labetalol in the intervention group when hyperdynamic hypertension is assumed (MAP/HR ratio ≤ 1.1), and slow-release nifedipine when hypodynamic hypertension is assumed (MAP/HR ratio ≥ 1.4). Women with normodynamic hypertension will be identified by a MAP/HR ratio between 1.1 and 1.4 and will be prescribed methyldopa (Fig. 5). Treatment will be increased if the targeted blood pressure of < 130/80 mmHg (MAP 97 mmHg) is not achieved [7, 30]. The maximum dosages for blood pressure control are 800 mg three times daily for labetalol, 30 mg three times daily for slow release nifedipine and 1000 mg three times daily for methyldopa. If the maximum dosage has been administered and the MAP/HR ratio does not indicate another medication class, the blood pressure will be accepted. Moreover, in the unlikely event that blood pressure measurements fall below 95/50 mmHg, the treatment regime will be reduced and the last added medication step will be stopped. In case of intolerable side effects, the medication class will be switched; methyldopa will substitute labetalol or nifedipine, and nifedipine will substitute methyldopa when the MAP/HR ratio is ≥1.3 and labetalol when the MAP/HR ratio is < 1.3. Antihypertensive drugs will be provided by the local pharmacy. Since this is an open-label study, the participant, researcher, and physician will know the type and dosage of the prescribed medication. Adherence to the treatment and side effects of the medication in the intervention group will be discussed and recorded during each scheduled check-up.

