### Planned statistical analysis

The effectiveness of haemodynamically tailored treatment of mild to moderate gestational hypertension will be evaluated based on the intention-to-treat principle. Descriptive statistics will be used to compare baseline characteristics between study groups. The primary analysis will be an X^2^ test, or Fisher’s exact test in groups with less than five cases, to compare the incidence of severe hypertension and preeclampsia in the intervention group and the control group. We planned to conduct a per protocol sub-analysis in with women with at least 80% of their medication intake assessed by self-report at each pregnancy check-up. Secondary outcomes will be assessed by using X,^2^ Fisher’s exact test, Mann-Whitney U or T test as appropriate. For both primary and secondary outcomes, crude and adjusted odds ratio’s will be calculated (control group will be considerate as reference) and adjustments will be made for gestational age at recruitment. Separate analyses will be conducted to evaluate whether or not optimal blood pressure control was reached, if the type of medication and dosage affected the outcomes, which haemodynamic profiles were most prevalent, and if the initial haemodynamic profile affected the outcome, and to explore the effect of BMI, parity and age on the haemodynamic profile and response to medication.

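### The nifedipine threshold is justified by a likelihood above 95% at a MAP/HR ratio of 1.4, but the protocol's own inputs give about 87% there and reach 95% only near 1.49

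*Protocol article*

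**What the plan says.** All of the relevant material is in the Interventions section of the protocol article.

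- Resistance is defined by formula: "Total peripheral vascular resistance (calculated as: 80 × MAP / cardiac output"), with cardiac output given as stroke volume times heart rate.
- The cut-off for vasoconstriction is stated: "Women can be considered vasoconstricted when gestational vascular resistance exceeds 1300" dyne.s/cm⁵.
- The ratio leaves out stroke volume, for which the section gives a distribution: "During healthy pregnancy, the mean ± SD stroke volume is 75 ± 10 ml".
- The method for linking the ratio to resistance is "we can estimate the range in which total peripheral vascular resistance must be by taking the mean ± 2 SD stroke volume".
- The result is "When the MAP/HR ratio exceeds 1.4, more than 95% of all women must be considered vasoconstrictive".
- That result is then attached to the threshold itself: "we assumed a likelihood of more than 95% vasoconstrictive and relatively hypodynamic, corresponding a MAP/HR ratio 1.4 as reference value for considering vasodilating medication".
- The treatment rule follows, with "slow-release nifedipine when hypodynamic hypertension is assumed", meaning a ratio of 1.4 or more. Ratios between 1.1 and 1.4 lead to methyldopa.

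The section also says that no empirical data were available for choosing the cut-offs. The Planned statistical analysis section lists separate analyses of "which haemodynamic profiles were most prevalent, and if the initial haemodynamic profile affected the outcome".

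**The concern.** The section supplies every quantity needed to check the 95% figure, and the figure does not come out. Because the protocol acknowledges that the cut-offs have no empirical basis, this likelihood is the only numerical argument for the point at which a woman moves from methyldopa to nifedipine. Drug choice by haemodynamic profile is the intervention under test, so the reasoning behind the threshold should be right.

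If the figure is too high, women with ratios of about 1.40 to 1.49 are assigned nifedipine with less certainty about their profile than the protocol intends. Readers of the planned results by profile may also take the ratio to be a sharper classifier than it is.

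**Working it through.** **Inputs (all from Interventions).** Resistance = 80 × MAP / cardiac output, with cardiac output in l/min. Cardiac output = stroke volume × HR. Limit for vasoconstriction: 1300. Stroke volume: mean 75 ml, SD 10 ml.

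**Formula.** Substituting, with stroke volume SV in ml:

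resistance = 80,000 × (MAP/HR) / SV

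A woman with ratio r is therefore vasoconstricted when SV < 80,000 × r / 1300.

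**Step 1: the protocol's own method at 1.4.** The mean ± 2 SD range of stroke volume is 55 to 95 ml.

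| Stroke volume (ml) | Resistance at ratio 1.4 |
|---|---|
| 55 | 80,000 × 1.4 / 55 = 2036 |
| 75 | 80,000 × 1.4 / 75 = 1493 |
| 95 | 80,000 × 1.4 / 95 = 1179 |

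The range runs from 1179 to 2036 and crosses 1300, so the stated rule is not met at 1.4. No distributional assumption is needed for this. The rule is first met at 1300 × 95 / 80,000 = 1.544.

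**Step 2: the likelihood.** Assume that stroke volume is normal and independent of the ratio; the protocol states neither. At 1.4 the critical stroke volume is 80,000 × 1.4 / 1300 = 86.15 ml, so z = (86.15 − 75) / 10 = 1.115 and the probability of vasoconstriction is 0.868.

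| MAP/HR ratio | Critical SV (ml) | Vasoconstricted |
|---|---|---|
| 1.40 | 86.15 | 86.8% |
| 1.45 | 89.23 | 92.3% |
| 1.486 | 91.45 | 95.0% |
| 1.50 | 92.31 | 95.8% |
| 1.60 | 98.46 | 99.0% |

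The 95% point is 1300 × (75 + 1.645 × 10) / 80,000 = 1.486. Rounding does not explain the gap, since even 1.45 falls short.

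**Step 3: does the model fit the protocol's other statement?** At 1.1 the critical stroke volume is 67.69 ml and 76.8% are vasodilated. This agrees with the statement that more than half are, so only the 1.4 figure fails.

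**Step 4: sensitivity to distributional shape.** Keeping mean 75 and SD 10, the value at 1.4 is 82.2% (uniform), 85.2% (triangular), 86.6% (gamma), 86.7% (lognormal), 88.3% (logistic) and 89.5% (t with 5 df). None reaches 95%.

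**Step 5: what would give 95% at 1.4.** Changing one input at a time:

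- mean stroke volume of 86.15 − 1.645 × 10 = 69.7 ml;
- or SD of (86.15 − 75) / 1.645 = 6.8 ml;
- or resistance limit of 80,000 × 1.4 / 91.45 = 1225.

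The section gives none of these.

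**Step 6: the alternative reading, averaging over all women above 1.4.** This needs a distribution of the ratio, which the protocol does not give. Assuming it is normal with mean 1.2, 1.3 or 1.4 and SD 0.15, 0.20 or 0.25, the average runs from 92.8% (mean 1.2, SD 0.15) to 96.8% (mean 1.4, SD 0.25). Six of the nine combinations reach 95%. Under the same assumptions, 27% to 69% of the women above 1.4 lie below 1.486.

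**The case against.** The strongest reply is that the first sentence concerns women whose ratio exceeds 1.4, not a woman at 1.4. Read as an average over that group, it may well be true, as step 6 shows. This reading cannot be excluded for that sentence alone. It does not rescue the later sentence, which attaches the 95% to 1.4 as the reference value, and it is not the method described, which takes a range of stroke volume at a given ratio. Even with an average of 95%, women just above 1.4 would be near 87%.

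Other points carry some weight:

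- **Assumptions.** Normality and independence are ours, so 87% and 1.49 depend on them. The failure of the mean ± 2 SD rule does not.
- **Population.** The stroke volume figures describe healthy pregnancy, while the algorithm is used in hypertensive women. The true likelihood at 1.4 could lie on either side of 87%.
- **Fig. 4.** It could not be seen and may carry further inputs.
- **Clinical consequence.** Between 1.40 and 1.49 vasoconstriction remains by far the likelier state (87% to 95%). The Background names calcium channel blockers and central-acting alpha agonists alike as options for high resistance. The worked examples show medication being revisited with the ratio at follow-up. The protocol also accepts a likelihood of just over one half for labetalol.
- **Analysis.** Nothing in the planned analysis uses the 95% as an input.

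These points limit the consequences. They do not make the stated figure agree with the stated inputs.

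**Conclusion.** The concern holds. By the protocol's own inputs and method, a ratio of 1.4 does not secure vasoconstriction in more than 95% of women. With normal stroke volume independent of the ratio the likelihood at 1.4 is about 87%, and 82% to 90% across the other shapes tried. The 95% level needs a ratio of about 1.49, and the mean + 2 SD rule about 1.54.

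The error is confined to the rationale for the nifedipine threshold and to how results by profile are read. It does not show that 1.4 is a poor clinical choice. The randomised comparison, the primary endpoint and the sample size do not depend on it. The 1.1 statement is correct, and no likelihood is claimed for the 1.3 switching rule, so neither is in question. The point should be fixed because a figure the treatment algorithm relies on is wrong as written and is cheap to correct.

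**What to change.** Correct the 1.4 figure in both sentences of Interventions that carry it. Suggested text:

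> At a MAP/HR ratio of 1.4, about 87% of women are expected to be vasoconstricted (resistance above 1300), assuming stroke volume is normally distributed (75 ± 10 ml) and independent of the ratio; 95% is reached at about 1.49.

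Alternatively, if the 95% came from other inputs, such as a lower stroke volume in hypertensive women, state those inputs and show that they give 95% at 1.4. In either case, reconcile the text with Fig. 4 and use the corrected likelihood when interpreting results by haemodynamic profile.

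The clinical team should record whether 1.4 is acceptable at about 87% or whether the intended 95% calls for about 1.49. Leave the 1.1 and 1.3 text unchanged.

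The cost is low: one recalculation, two sentences and a figure check. Keeping 1.4 changes nothing in trial conduct; moving it would be an amendment to the treatment algorithm.

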#### Secondary and other study parameters

Maternal outcomes: side effects of medication, required level of care, serious maternal complications (maternal death, HELLP syndrome defined as the combination of thrombocytopenia, elevated transaminases and haemolysis, stroke, blindness, uncontrolled hypertension, respiratory failure, myocardial ischaemia/infarction, renal failure, hepatic haematoma and/or rupture, coagulopathy), birth-related variables, and placental abruption.

Neonatal outcomes: miscarriage, gestational age at delivery, birth weight and centile, Apgar score at 1 and 5 min after birth, use of antenatal corticosteroids and surfactant, adverse perinatal outcomes (miscarriage, stillbirth, neonatal mortality, and serious morbidity including neonatal sepsis, central nervous system morbidity and necrotizing enterocolitis), required level of care, and duration of care.

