### Data collection

Data will be recorded in predesigned case record forms. Data on pregnancy and neonatal outcomes will be collected from the hospital maternity records. Additional neonatal outcomes will be collected from the discharge summary when neonates are admitted to the neonatal care department.

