### Sample size / power calculation

Severe hypertension and preeclampsia develop respectively in 20% and 15–25% of women initially diagnosed with mild to moderate gestational hypertension [6, 32]. As severe hypertension and preeclampsia require comparable in-hospital treatment, we consider an 15% reduced incidence of both as clinically relevant. We calculated the sample size based on a progression level of 10% in the intervention group and a progression level of 25% in the control group. For a desired power of 80% and a two-tailed alpha level of 0.05, we need to recruit 99 women per group. Considering an anticipated dropout rate of 5%, we will recruit 208 women for randomization. We expect to include approximately 160 women who do not consent for randomization but agree to follow-up of their pregnancy outcomes. In this observational cohort, we will evaluate general obstetrical care for mild to moderate hypertension, patient characteristics, and patient outcomes comparable to the randomized population.

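### Side effects of medication fall under the planned odds ratios against control, but the only stated recording procedure covers the intervention group, so that contrast is not interpretable as written

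*Protocol article*

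**What the plan says.** Four parts of the protocol article bear on this point.

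- **Outcome.** Under Secondary and other study parameters, side effects come first among the maternal items: "Maternal outcomes: side effects of medication, required level of care, serious maternal complications".
- **Analysis.** Planned statistical analysis assigns secondary outcomes to a chi-square test or "Fisher’s exact test, Mann-Whitney U or T test as appropriate". It then adds: "For both primary and secondary outcomes, crude and adjusted odds ratio’s will be calculated (control group will be considerate as reference". Side effects are not exempted from either statement.
- **Recording.** The last sentence of Interventions gives the only procedure stated for collecting side effects: "Adherence to the treatment and side effects of the medication in the intervention group will be discussed and recorded during each scheduled check-up".
- **Exposure.** The abstract says of the comparator: "Women randomized to the control group will receive non-pharmacological standard care according to national and international guidelines". Trial design and setting adds that once severe hypertension or preeclampsia is diagnosed, usual care means "intensifying or initializing antihypertensive medication for the intervention group and control group, respectively".

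The trial is open-label.

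**The concern.** A between-arm odds ratio is informative about harm only if the event can occur, and is looked for in the same way, in both arms. Here the event is defined by its attribution to a drug, control women have no study drug, and regular questioning is described for treated women only. Because the trial is open-label, a complaint from a treated woman is also easily attributed to her tablets, while the same complaint from a control woman has no drug to be attributed to.

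What is at stake is the tolerability side of the benefit-harm balance. The trial asks whether to medicate women who would otherwise be managed without drugs. A reader will want to know whether treated women feel worse than untreated women, and the planned analysis would give a number that appears to answer this but does not.

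**Working it through.** The plan states no figure for side effects, so there is none to reproduce. Its sample size enters only through the number per arm. With 25% versus 10%, 80% power and two-sided 5%, the unpooled formula gives (1.960 + 0.842)² × (0.25 × 0.75 + 0.10 × 0.90) / 0.15² ≈ 97 per group, and the pooled version gives 100. The stated 99 is consistent with these and is not in question. Randomizing 208 women 1:1 gives 104 per arm.

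**Case A: no side effects captured in controls.**

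- With x events among 104 treated women and 0 among 104 controls, the crude odds ratio is x × 104 / [(104 − x) × 0], which is infinite for any x > 0. The ordinary adjusted logistic odds ratio likewise has no finite maximum-likelihood estimate.
- With equal arms, the two-sided Fisher p-value is 2 × C(104, x) / C(208, x). For 5 versus 0 it is 0.060, for 6 versus 0 it is 0.029, and for 10 versus 0 it is 0.0016.
- Adding 0.5 to each cell for 10 versus 0 gives (10.5 × 104.5) / (94.5 × 0.5) = 23.2, with a 95% interval of 1.3 to 402.

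**Illustration of ascertainment alone.** Assume that the background complaint rate is the same in both arms, that the drugs have no effect, and that every complaint in a treated woman is written down as a side effect. The documents give no such rate, so a range is shown.

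| Assumed rate | Recorded in one arm | Fisher p | Recorded in both arms | Odds ratio |
|---|---|---|---|---|
| 5% | 5 v 0 | 0.060 | 5 v 5 | 1 |
| 10% | 10 v 0 | 0.0016 | 10 v 10 | 1 |
| 20% | 21 v 0 | 3 × 10⁻⁷ | 21 v 21 | 1 |

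**Case B: side effects captured in controls who start a drug after progressing.** Sample size / power calculation assumes a "progression level of 10% in the intervention group and a progression level of 25% in the control group". That implies 0.25 × 104 = 26 control women who would usually start medication. Assume that a proportion s of drug-exposed women have a side effect, that s is the same in both arms, and that all such events are captured. The control proportion is then 0.25 × s.

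| Assumed s | Expected control events | Odds ratio |
|---|---|---|
| 10% | 104 × 0.025 = 2.6 | (0.10/0.90) / (0.025/0.975) = 4.3 |
| 20% | 104 × 0.050 = 5.2 | (0.20/0.80) / (0.050/0.950) = 4.8 |
| 30% | 104 × 0.075 = 7.8 | (0.30/0.70) / (0.075/0.925) = 5.3 |

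The odds ratio is now finite, but it hardly depends on how often the drugs cause side effects. The risk ratio is s / (0.25 × s) = 4 whatever s is, which is simply the inverse of the share of controls exposed to a drug. The contrast measures exposure.

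**The case against.** The strongest reply is that this reads a condensed article too literally. The recording sentence stands under Interventions, is paired with adherence, and may only describe how women on study drug are monitored. It does not say that control symptoms go unrecorded. The schedule figures and the case record forms are not visible. The tests apply as appropriate, and the odds-ratio sentence also covers items such as birth weight and duration of care, for which a group odds ratio is not defined without dichotomizing. It therefore may not bind every item. The stated secondary objectives do not name side effects.

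Much of this stands, and it rules out several stronger conclusions that a reader might draw:

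- **That side effects are recorded only in the intervention arm.** The text names that arm but excludes no other. Data collection also says "Data on pregnancy and neonatal outcomes will be collected from the hospital maternity records", with no restriction by arm.
- **That the control count must be zero and the odds ratio infinite whatever the truth.** Controls who progress usually start antihypertensives, so events are possible, as Case B shows.
- **That maternal harm cannot be assessed at all.** Serious maternal complications, placental abruption and level of care are listed for both arms. Severe headache and persistent visual scotomata are among the preeclampsia criteria, so they matter for the primary endpoint in both arms.

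The illustrative rates are also assumptions, not trial figures.

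The reply does not remove the conflict between what the article does state: a drug-defined outcome, a control-referenced odds ratio with no exemption, and one described procedure covering one arm. Passive review of maternity records is not equivalent to asking at every check-up, and capturing events in progressing controls replaces an inestimable ratio with one that tracks exposure.

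**Conclusion.** The point holds as a limited one. As written, the control-referenced odds ratio for side effects of medication is either not estimable (no control events captured) or mainly reflects drug exposure and unequal ascertainment (some captured). In neither case does it show whether treated women have more symptoms than untreated women.

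On size: if symptoms were captured in one arm only, 6 or more events out of 104 would be nominally significant, and a 10% background rate with no drug effect would give p = 0.0016. If events in progressing controls were captured, the odds ratio would be about 4.3 to 5.3 over assumed side-effect rates of 10% to 30%. These figures rest on 104 women per arm, the planned 25% control progression and the assumed rates. The conclusion that the contrast is uninterpretable does not depend on the particular rates.

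The change should be made, but it concerns one secondary outcome. The primary endpoint, the sample size and the comparison of serious maternal complications are not affected.

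**What to change.** Choose one of two changes.

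1. **Make the comparison valid.** Record the same short symptom checklist in both arms at each scheduled check-up, and compare all symptoms between arms regardless of presumed cause. The cost is one short checklist on the existing case record form, at check-ups that women in both arms already attend.
2. **Drop the comparison.** State in Planned statistical analysis that side effects of medication are exempt from the between-group tests and odds ratios and will be reported descriptively for the intervention arm, by drug, with no comparative claim. The cost is one sentence.

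The first option answers the tolerability question. The second only prevents a misleading number. Neither changes treatment.
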